#### Emotion regulation

This will be measured by the Emotion Regulation Questionnaire for Children and Adolescents (ERQ-CA) [76]. This a 10-item measure assessing individuals’ propensity to use cognitive reappraisal (6-items) and expressive suppression (4-items) as emotion regulation strategies. Items are rated on a 5-point scale, ranging from Strongly disagree (1) to Strongly agree (5). Items are summed on each subscale to produce total scores; cognitive reappraisal ranging from 6 to 30 and expressive suppression ranging from 4 to 20. Higher scores on each subscale reflect greater use of the corresponding emotion regulation skill. The measure has shown good psychometric properties for the assessment of emotion regulation strategies in children and adolescents [76].

#### CBT skill acquisition

This will be measured by the Cognitive Behavioural Therapy Skills Questionnaire (CBTSQ) [77]. The CBTSQ is a 16-item scale assesses the frequency of individuals’ use of cognitive behavioural skills. The measure is composed of two subscales measuring cognitive restructuring skills (9-items) and behavioural activation strategies (7-items). Items are rated on a 5-point scale, ranging from I don’t do this (1) to I always do this (5). Items are summed on each subscale to produce a total score for cognitive restructuring (range: 9 to 45) and for behavioural activation (range: 7 to 35). Higher scores on the subscales indicate greater use of CBT skills. The CBTSQ has good psychometric properties [77] and has been used in adolescent populations [78].

#### Demographics

Participants will be asked their gender identity (female, male, non-binary, different identity, free response option), whether they identify as Aboriginal or Torres Strait Islander (yes, no, prefer not to say), whether they identify as Lesbian, Gay, Bisexual, Transgender, Queer and/or Intersex (yes, no, I’d prefer not to say), their Australian state or territory location (New South Wales [NSW], Queensland [QLD], Victoria [VIC], Tasmania [TAS], South Australia [SA], Western Australia [WA], Northern Territory [NT], Australian Capital Territory [ACT]), location description (metropolitan, regional, or rural/remote), their date of birth, school grade (Years 7, 8, 9, 10, 11, 12, not currently in school) and the type of mobile device they use (iOS [e.g., Apple], Android [e.g., Samsung], other). Participants will also be asked how they heard about the study (e.g., social media, BDI website, word of mouth, other) and their motivations for participating (e.g., need for mental health care, desire to contribute to a broader social good, parents/carers encouragement, friend participating, financially motivated, desire to help research, interest in learning about mental health or other).

#### Recent mental health care

At baseline participants will be asked to report whether they have ever been diagnosed with anxiety or depression by a health professional (yes - depression only, yes - anxiety only, yes -both depression and anxiety, no, I don’t know, I’d rather not say), whether they have ever received psychological treatment for a mental health problem or mental illness from a health professional (yes, no, I’d rather not say) and whether they have ever taken prescribed medication for a mental health problem or mental illness like depression or anxiety (yes, no, I’d rather not say). At the primary and secondary endpoints participants will be asked to report whether throughout the study they were diagnosed with depression or anxiety by a health professional (yes - depression only, yes - anxiety only, yes -both depression and anxiety, no, I don’t know, I’d rather not say), whether they received psychological treatment from a health professional (yes, no, I’d rather not say), starting taking prescribed medication for a mental health problem or mental illness (yes, no, I’d rather not say) or felt like they needed help for a mental health issue like depression or anxiety (yes, no, I’d rather not say).

#### Previous use of mobile apps for mental health

Participants will be asked to report whether they have ever used any mobile app to help with their emotional wellbeing or mental health (yes, no, I’d rather not say), and if yes, whether they found it helpful (yes, no). Participants will also be asked how much they think their emotional wellbeing could be improved by using a mental health smartphone app on a 5-point scale ranging from not at all (1) to extremely (5).

#### Perceived need and help-seeking barriers

This will be measured by the Perceived Need for Care Questionnaire (PNCQ). The PNCQ is a four-item measure designed to determine an individuals’ perceived need for mental health care. Perceived need is assessed across four domains of adolescent mental health care: counselling, medication, information, and skill training. Each domain is assigned one of four levels of perceived need (need fully met, need partially met, need unmet, or no need) using the information provided regarding whether sufficient care was received. If perceived need is not fully met, participants select the type of help needed (e.g., counselling, medication, information, and skill training) and the barriers (e.g., self-reliance, stigma, accessibility, financial reasons) kept them from receiving adequate care. Barriers are categorised as attitudinal or structural (e.g., “Couldn’t get an appointment when needed [structural]” and “Wanted to work out the problem on my own [attitudinal; self-reliance]”) [15]. The instrument has good psychometric properties [79] and has been adapted for use in large representative samples of adolescents [80, 81].

#### Digital therapeutic Alliance (digital working Alliance inventory)

This will be measured by the Digital Working Alliance Inventory (DWAI) [82]. The DWAI is a 6-item measure adapted from the Working Alliance Inventory- short version to assess the therapeutic alliance between an individual and digital intervention (WAI-SF) [83, 84]. The measure assesses three core domains: goals (e.g., I trusted the app to guide me towards my personal goals), tasks (e.g., I believed the app tasks will help me to address my problem) and bond (e.g., The app encouraged me to accomplish tasks and make progress). Each item is rated on a 7-point scale ranging from strongly disagree (1) to strongly agree (7). Items are summed to produce a total score (range: 6 to 42). Higher scores reflect higher levels of digital working alliance with the program. The original scale has good psychometric properties [83, 84], and preliminary evidence of the DWAI’s psychometric properties is positive, however it is yet to undergo rigorous psychometric evaluation [85].

#### Digital program satisfaction

This will be assessed using an 11-item measure adapted from previous digital mental health research [59]. The measure is designed to assess participants’ satisfaction, experience and perceived helpfulness of the intervention received. For the first eight items on the scale, participants are asked to agree or disagree with a set of statements that assess aspects of their satisfaction and experience with the intervention. The measure also includes a helpfulness item, where participants are asked to rate the overall helpfulness of the intervention on a 5-point scale ranging from extremely unhelpful (1) to extremely helpful (5). The final two free response questions examine how ClearlyMe® or the psychoeducation flyers were helpful (e.g., In what ways did ClearlyMe help you?) and provide participants with the opportunity to suggest improvements (e.g., What would make ClearlyMe better?).

#### SMS chat feedback

The SMS Chat Feedback questionnaire is an 8-item measure that was adapted from [86] by the study authors to gain feedback on the SMS chat support provided to participants in the guided support condition. The first item on the scale asks participants whether they participated in the SMS chat support (yes, no). Participants who respond ‘no’ are asked what stopped them participating (free response). Participants who respond ‘yes’ are asked seven additional questions. Five are rated on a 5-point scale and assess how much participants liked the SMS chats (disliked a lot [1] to liked a lot [5]), perceived helpfulness for encouraging use of ClearlyMe® (extremely unhelpful [1] to extremely helpful [5]), convenience of the timing (extremely inconvenient [1] to extremely convenient [5]), and their level of satisfaction with the frequency and length of the SMS chats (not at all satisfied [1] to extremely satisfied [5]). Participants will also be asked two free response questions about what they liked or disliked about the SMS chats and how the SMS chats could be improved.

#### Digital program barriers

The Digital Program Barriers questionnaire is a 14-item measure was adapted from previous digital mental-health research conducted by researchers of this study [59]. This measure is designed to examine any barriers or difficulties that participants experienced accessing or using the ClearlyMe® app or the psychoeducation flyers. Each item requires participants to select “yes” or “no” in response to a statement describing a barrier, including technical issues, accessibility and individual factors.

#### Engagement – ClearlyMe®

The current study utilises and will report multiple measures of engagement, consisting of ‘uptake’, ‘adherence’, and ‘completions’. In the current study, ‘uptake’ is defined as the proportion of participants (%) who take up the app, measured by app downloads. ‘Adherence’ is defined as the proportion (%) of participants who followed the instructions for app use. This will be measured in two ways: 1) A categorical variable (adherers vs. non-adherers) in which participants who complete at least one collection each week for the entire 6 weeks will be deemed ‘adherers’; 2) A numerical variable in which participants will earn 1 point for each week that they adhered to the instructions (i.e., completed at least one collection) resulting in a total adherence score (range: 0 to 6). ‘Completions’ is used to describe participants’ exposure to the app content, measured in three ways: 1) the number of lessons completed as a proportion of the total number of lesson, 2) the proportion (%) who completed more than half of the app content (i.e, 19 of 37 lessons), 3) the proportion (%) that completed all of the app content (i.e., all 37 lessons). Additional exploratory data will be collected to describe participants’ use of the ClearlyMe® app: collections completed (out of 9), the total number of times app features are accessed (e.g., Stories, View all, Get help now, Mood check, Saved), time spent in app (minutes), the collections and lessons liked/disliked, the collections and lessons saved, and individual responses to the lesson activities. Different measures of engagement have been employed to move beyond the pervasive conceptualisation of engagement as the ‘more use, the better’ in acknowledgement that there are multiple ways participants may engage with the intervention [38, 87, 88]. Recommendations have been followed [88] to include measures frequently used in the literature (e.g., proportion of lessons completed), intervention specific measures (e.g., frequency of feature access) and a measure of adherence defined as the extent to which actual use aligns with instructions for use. This allows a deeper analysis of the most beneficial way to use ClearlyMe® and supports comparisons with other studies given the heterogeneous reporting of engagement [36, 38, 88].

#### Engagement – control condition

For participants allocated to the control condition, the number of times each psychoeducation flyer is accessed via the URLs in the weekly SMSs will be recorded for each participant and include time and date of access.

### Sample size

The total sample size required for detecting change in the primary outcome at the primary endpoint was calculated to be 489. This was based α = 0.05, power = 0.8, small to medium within-group effect sizes for psychoeducation (d = 0.10) [40, 41], self-directed CBT (d = 0.35) [89], and guided CBT (d = 0.65) [18, 19] on depressive outcomes and a conservative attrition rate of 20% between baseline and primary endpoint. This sample size will also be sufficient to detect small between-group effect sizes between the intervention conditions and the attention control condition and between the self-guided and supported use intervention conditions.

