Low engagement with digital CBT among adolescents does not appear to be due to their unwillingness to use digital technologies to address mental health concerns. Uptake of commercially developed mental health smartphone apps is substantial, with millions of downloads and thousands of active monthly users [25]. Despite widespread uptake, many commercially developed apps lack both proof of effectiveness and critical CBT elements [26]. Among evaluated mental health smartphone apps, two recent reviews collectively identified only three smartphone apps for adolescents that contained elements of CBT, with none specifically targeting adolescent depression [27, 28]. Young people have reported that many of the existing computerised CBT interventions are less visually appealing than commercially developed apps, with unrefined usability and content that is not aligned with their needs [20]. This may explain why comparisons of studies show smartphone mental health apps outperform computerised and web-based interventions in terms of engagement, with an average retention rate of 80% [28] compared to 57% [18], although there is substantial variability in completion rates between apps. Given high rates of ownership and uninhibited access to internet and multimedia functionality, smartphones offer a promising means of delivering CBT that is yet to be adequately exploited.

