### Strengths

The design of the MobiliseMe trial is robust. First, the inclusion of an active-attention matched control condition will allow an evaluation of the impact of ClearlyMe® over and above the support young people commonly receive when help-seeking independently, that is, information about mental symptoms and treatment options [93]. Second, a comparison condition that involves using ClearlyMe® with SMS guidance is well-matched to the needs of young people [31, 32] and will provide much needed knowledge on the influence of guidance on engagement and effectiveness. Third, the sample size (*N* = 489) of the trial will ensure adequate power to detect intervention effects. Finally, a thorough consideration of ‘engagement’ and transparent reporting of how constructs such as uptake, adherence and completion have been operationalised, measured and analysed addresses a well-documented limitation in the field [22, 67, 88, 94].

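### The stated inputs do not support the claim that 489 participants suffice for small between-group effects: on the change-score scale, power is about 52% for self-directed vs control and 67% for guided vs self-directed

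*Protocol article*

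**What the plan says.** The Sample size section of the protocol article gives the target: "The total sample size required for detecting change in the primary outcome at the primary endpoint was calculated to be 489". The inputs are alpha 0.05, power 0.8, "small to medium within-group effect sizes for psychoeducation (d = 0.10) [40, 41], self-directed CBT (d = 0.35) [89", a within-group value of 0.65 for guided CBT, and 20% attrition to the primary endpoint.

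It then makes a second, affirmative claim: "This sample size will also be sufficient to detect small between-group effect sizes between the intervention conditions and the attention control condition". The sentence goes on to cover self-guided against supported use as well. No number is attached to small.

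Under Strengths, the article says that the sample size "of the trial will ensure adequate power to detect intervention effects".

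Two other sections bear on this. Hypotheses frames the primary question as app (self-directed or guided) against control. The statistical methods section tests the time-by-condition interaction in a mixed model and standardises effects by the SD of change pooled over conditions.

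**The concern.** The inputs describe how much each arm changes. The hypotheses and the test concern how much the arms differ in change. An arm that improves by 0.35 SD, set against a control that improves by 0.10 SD, differs from it by 0.25 SD and not 0.35, provided both use the same standardiser. The section never makes this step, yet it asserts that the between-group comparisons are covered.

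The comparison most exposed is self-directed use against control. It is one of the two app conditions named in the primary hypothesis, and the Background introduces the app as a free, self-directed product. If its power is well below 80% on the plan's own assumptions, a non-significant result could be misread as coming from a trial with assured power.

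**Working it through.** **Inputs.** From Sample size: alpha 0.05, power 0.80, within-group effects 0.10, 0.35 and 0.65, attrition 20%. From Trial design: equal allocation over three arms, so 489/3 = 163 randomised per arm and 163 × 0.8 = 130.4, taken as 130 evaluable. Two-sided testing is assumed, since sidedness is not stated.

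**Formula.** Two-sample t-test with n per arm: power is the probability that a noncentral t variable with 2n − 2 degrees of freedom and noncentrality d√(n/2) exceeds the 5% two-sided critical value.

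**Step 1: reproduce 489.** Taking d = 0.35 as a between-group effect, 129 per arm gives just under 80% and 130 gives 80.3%. Then 130/0.8 = 162.5, rounded up to 163, and 163 × 3 = 489. The match is exact.

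The effects taken as labelled do not give 489:
- paired tests at 0.10, 0.35 and 0.65: totals of 2952, 252 and 81;
- three-arm F-test on change (f = 0.225): 65 per arm, 82 after attrition, total 246;
- pairwise differences of 0.25, 0.30 and 0.55: totals of 951, 660 and 201.

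The match is not unique. At d = 0.25, 253 per arm are needed without adjustment. Baseline adjustment at correlation r = 0.70 multiplies this by 1 − 0.70² = 0.51, giving 129.03, so 130 per arm and again 489. No correlation is stated.

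**Step 2: implied contrasts on the change-score scale.** Self-directed vs control: 0.35 − 0.10 = 0.25. Guided vs self-directed: 0.65 − 0.35 = 0.30. Guided vs control: 0.65 − 0.10 = 0.55. Pooled app vs control: (0.35 + 0.65)/2 − 0.10 = 0.40.

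**Step 3: power with 130 evaluable per arm.** √(130/2) = 8.062.

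| Contrast | d | Noncentrality | Power |
|---|---|---|---|
| Conventional small effect (assumed) | 0.20 | 1.61 | 36% |
| Self-directed vs control | 0.25 | 2.02 | 52% |
| Guided vs self-directed | 0.30 | 2.42 | 67% |
| Guided vs control | 0.55 | 4.43 | 99% |
| Pooled app vs control (260 vs 130) | 0.40 | 3.72 | 96% |

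The smallest d detectable at 80% power is about 0.35. For 80% power, d = 0.25 needs 253 evaluable per arm (253/0.8, rounded up to 317; total 951). For d = 0.30 the figure is 176 (220 randomised per arm; total 660).

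**Step 4: if the effects are in baseline-SD units.** Assume equal variances and correlation r between baseline and 6 weeks. The relevant SD is then √(2(1 − r)) for a change analysis and √(1 − r²) for a baseline-adjusted one. The range r = 0.5 to 0.7 is an assumption.

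| d | Change analysis | Baseline-adjusted |
|---|---|---|
| 0.20 | 36–55% | 46–61% |
| 0.25 | 52–74% | 64–80% |
| 0.30 | 67–88% | 79–92% |

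Reaching 80% at d = 0.25 needs r of about 0.74 (change) or 0.70 (adjusted). At d = 0.30 it needs about 0.63 or 0.51.

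**The case against.** The strongest objection is that the shortfall depends on a scale that the Sample size section does not name. Published within-group effects may be standardised by the baseline SD. With a good correlation and a baseline-adjusted model, 0.25 then reaches 80% at r = 0.70, and 0.30 reaches about 80% or more over most of the range. This stands: 52% and 67% are conditional figures and should be quoted as such. It does not rescue the claim. No correlation is given, the statistical methods section standardises by the SD of change, and under a change analysis the 0.25 contrast misses 80% unless r is about 0.74 or higher.

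A second objection is that small is undefined and could be stretched to 0.35. At 0.35 in change-score SD units the sentence would be true. The plan's own inputs, however, imply smaller differences for two of the comparisons that the sentence covers. At 0.20, power falls short on either scale across r = 0.5–0.7.

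Third, much of the trial is well powered. If the primary hypothesis is read as both app arms pooled against control, power is about 96%, and guided vs control has 99%. The protocol also makes no hypothesis about the effect of guidance on outcomes. All of that is correct and narrows the point. The sufficiency sentence nevertheless names the intervention conditions against control and, separately, self-guided against supported use.

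**Conclusion.** The sufficiency sentence is wrong as written. In change-score SD units, with two-sided 5% tests and 130 evaluable per arm, power is about 52% for self-directed vs control and 67% for guided vs self-directed, and the detectable effect is about 0.35. In baseline-SD units the shortfall is smaller and can disappear, but only with a correlation that the protocol does not state.

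Four stronger readings are tempting, and the document does not support them:
- That 0.35 was mistakenly used as a between-group effect and the control arm's 0.10 forgotten. The exact match suggests it, but the text does not say so, and 0.25 with baseline adjustment at r = 0.70 gives the same total.
- That the trial as a whole is underpowered. Guided vs control and pooled app vs control are not.
- That the joint power to win every contrast is the relevant measure. The protocol sets no such success criterion.
- That 20% attrition is not conservative because the Background reports apps "with an average retention rate of 80% [28] compared to 57% [18". Those figures concern engagement with interventions, whereas the 20% is loss from baseline to the 6-week assessment. Participants who never download the app stay in the trial.

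**What to change.** In Sample size, state the between-group effect, the SD scale, the assumed baseline-to-6-week correlation (if one was used) and the test that together give 489. Replace the sufficiency sentence with the detectable effect and the power for each contrast under the stated assumption. On the change-score scale this would read: 130 evaluable per arm give 80% power for a difference of about 0.35, and about 52%, 67% and 99% for differences of 0.25, 0.30 and 0.55. If the effects were in baseline-SD units, give the correlation and the corresponding figures instead.

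Under Strengths, limit the claim of adequate power to the contrasts that have it. Add that a non-significant self-directed vs control result will not be read as evidence of no effect.

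The cost is a less favourable stated power. The change is to wording only: it needs no extra participants and can be made although recruitment has begun.

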### Recruitment

Trial recruitment began on the 11th of May 2022, subsequent to submission of the trial protocol for peer-review. The first trial participant was enrolled on the 12th of May 2022. This study will utilise an online recruitment strategy. Study advertisements will be published on the Black Dog Institute website and social media channels (Facebook, Twitter, and Instagram) and provided to schools and organisations to share with their communities. Paid advertisements will be placed on social media sites (Twitter, Facebook, Instagram, Snapchat and Google). Online recruitment is an effective avenue to recruit generalised mental health samples [59, 90]. The research team will also contact relevant Australian mental health organisations and services to request distribution of study advertisements on their organisation’s communication channels (e.g., website, social media, newsletters, mailing list, in-person clinics). Study advertisements will also be emailed to individuals who have consented to being contacted about research studies conducted by the Institute. All study adverts will direct interested participants to the study website, where they will review the study information, and may choose to undertake screening, and provide consent using the provided links. Direct contact between the participant and study team is not required during recruitment and study enrolment. To ensure participant safety during recruitment, excluded participants are provided with contact information for Australian mental health and crisis support services and encouraged to seek help and speak to a trusted adult. The same information is provided to included participants immediately following consent, again at the end of the baseline survey and in the study welcome email. They are also encouraged to contact the research team if they have questions or are experiencing distress.

